## Abstract

**Background::**

Triple negative breast cancer affects 10% to 20% of all women diagnosed with breast cancer. Due to its characteristics, treatment strategies are limited and metastatic recurrences are common in the first 5 years after treatment. However, not all patients affected by this disease develop metastases. Tumor-infiltrating lymphocytes have shown to be reliable predictive biomarkers of treatment response and metastatic recurrences. However, we need to develop simpler and faster ways to predict response to cytotoxic treatment and the possibility of eventual cancer relapse by identifying new biomarkers. Recently, new studies are emerging, suggesting a predictive role of circulating blood cells in different types of cancer. In this study, we will assess the correlation between tumor-infiltrating lymphocytes and different elements of the blood count in patients diagnosed with triple negative breast cancer.

**Methods::**

The main objective of this study is to evaluate the correlation between the peripheral neutrophil-to-lymphocyte ratio and the amount of tumor-infiltrating lymphocytes, assessed in triple negative breast cancer patients at diagnosis. Secondary objectives include evaluation of the correlation between tumor-infiltrating lymphocytes at diagnosis and the baseline absolute neutrophil, lymphocyte, and platelet counts, as well as the platelet-to-lymphocyte ratio. The triple negative breast cancer patients will be enrolled in the PERCEPTION trial during the first year after the treatment completion. Two supplementary blood tests, at 12 months after the end of treatment and at the time of the first metastatic recurrence, will be performed.

**Discussion::**

The discovery of new prognostic and predictive biomarkers is crucial for triple negative breast cancer. We set up the PERCEPTION clinical trial in order to evaluate certain blood counts as early biomarkers and to assess their correlation with tumor-infiltrating lymphocytes. Demonstration of comparative predictive and/or prognostic capacities of peripheral blood counts and tumor-infiltrating lymphocytes would allow introduction of the former as simple and cheap biomarkers in triple negative breast cancer patient management.

**Trial registration::**

The PERCEPTION study has been registered in the French National Agency of Medical Security registry on the 2nd of July 2019 under the number 2019-A01861-56 and in the ClinicalTrials.org registry under the number NCT04068623.

## Introduction

1

Triple negative breast cancer (TNBC) represents 10% to 20% of all breast cancers. Treatment strategies for this type of breast cancer are limited, due to the lack of hormone receptor expression (oestrogen receptors and progesterone receptors) and the absence of amplification for the gene coding for the Human Epidermal Growth Factor Receptor 2 (HER2) protein, in tumor cells.^[1]^ As a result, patients diagnosed with TNBC cannot benefit from endocrine therapy or anti-HER2 therapy. Therefore, TNBC has an unfavorable prognosis with a high rate of metastatic recurrence during the first 5 years after treatment.^[2–4]^ However, not all TNBC patients develop metastatic recurrence and it is therefore crucial to identify biomarkers that would allow determining which patients will eventually relapse.

Several studies have demonstrated that higher amounts of tumor-infiltrating lymphocytes (TILs) in the biopsy before treatment are associated with higher rate of pathologic complete response (pCR) to the neoadjuvant chemotherapy (NACT).^[5]^ Other studies have shown a correlation between the presence of high TIL quantity in the surgical specimen after NACT and a better relapse-free survival, as well as a significantly reduced death rate, in patients suffering from TNBC.^[6,7]^ For instance, Dieci et al have found that the 5-year overall survival rate for patients with high quantities of TILs in the neoadjuvant chemotherapy setting was 91% and significantly higher than that of patients with low quantities of TILs whose 5-year overall survival rate was 55%.^[6]^

The assessment of TIL quantity in a cancer tissue specimen is a semi-quantitative method, which is still not in routine use due to the need for a highly skilled pathologist to perform it, and, also, due to certain level of the inherent error risk. Therefore, reliable quantitative biomarkers that are easy to measure and that could provide additional information to that of TILs or even replace them in predicting treatment response and disease relapse are still lacking.

Various blood cell counts and the ratios between them, such as neutrophil-to-lymphocyte ratio (NLR) and platelet-to-lymphocyte ratio (PLR) could be used as predictive biomarkers in several types of cancer, including breast cancer.^[1,8,9]^ The research conducted by Lee et al in 2019 suggests that low NLR at baseline is associated with a better overall survival in TNBC patients.^[1]^

Besides the full blood count, several studies have shown a correlation between the presence of circulating tumor DNA (ctDNA) in the blood and treatment response or even metastatic recurrence.^[10,11]^ Despite the insufficient data in TNBC, studies have shown that ctDNA is a reliable marker in predicting cancer recurrence, due to its high sensitivity and specificity.^[12,13]^ Moreover, this circulating biomarker can be obtained and quantified from a simple blood test. Therefore, evaluation of ctDNA as a predictor of metastatic relapse in TNBC is of great interest and it could provide additional information to that of TILs and/or the circulating blood cell counts.

## Patients and methods

2

### Study aim

2.1

The aim of this study is to evaluate the correlation between the absolute counts of blood neutrophils, lymphocytes, and platelets, as well as the NLR and PLR, and the amount of TILs assessed on hematoxylin and eosin (H&E)-stained breast tumor tissue sampled before treatment for women with TNBC. Evaluation of this correlation might provide important information whether peripheral blood counts and their ratios could replace TILs in the prediction of TNBC treatment response and metastatic recurrence. Another aim of this study is to assess ctDNA as a biomarker of metastatic cancer recurrence.

### Primary objective and endpoints

2.2

The primary objective of the PERCEPTION study is to evaluate the correlation between the amount of TILs found in the biopsy, measured semi-quantitatively as the percentage of tumor stromal area occupied by lymphocytes^[14]^ and the NLR derived from the absolute blood counts of neutrophils and lymphocytes in TNBC patients, at the time of diagnosis. The primary endpoints are the value of NLR and the amount of TILs at diagnosis (before any treatment). NLR is defined as the ratio of the absolute neutrophil count (ANC) over the absolute lymphocyte count (ALC) (NLR = ANC/ALC).

### Secondary objectives and endpoints

2.3

Secondary objectives of the present study include:

Assessment of the correlation between the amount of TILs in the biopsy and the total white blood cell count (WBC), ANC, ALC, absolute platelet count (APC), and PLR routinely assessed in women with TNBC, at diagnosis.Assessment of the correlation between the mentioned blood counts and their ratios (NLR and PLR), at the time of diagnosis, and the response to NACT according to Sataloff.^[15]^Assessment of the correlation between the mentioned blood counts and their ratios (NLR and PLR) at the time of diagnosis, and the TIL amount in the post-NACT surgical specimen.Assessment of the correlation between the mentioned blood counts and their ratios (NLR and PLR) and the recurrence-free survival (RFS).Assessment of the correlation between the mentioned blood counts and their ratios (NLR and PLR) before post-NACT surgery and TIL quantity in the surgical specimen post-NACT, depending on the time between surgery and the last administration of chemotherapy.Assessment of the correlation between the mentioned blood counts and their ratios (NLR and PLR) and the presence of ctDNA.Assessment of the correlation between ctDNA and RFS.Assessment of the correlation between the mentioned blood counts and their ratios (NLR and PLR) after cancer treatment and the RFS.

The secondary endpoints include the following:

The absolute values of total white blood cells, neutrophils, lymphocytes, platelets measured in number of cells × 10^12^/L and the PLR at diagnosis. PLR is defined as the ratio of the APC over the ALC (PLR = APC/ALC).The values of total white blood cells, neutrophils, lymphocytes, platelets, NLR, and PLR before post-NACT surgery.TIL amount in the biopsy before cancer treatment.TIL amount in the surgical specimen post-NACT.Response to NACT according to the Sataloff classification.The period of time between surgery and the last administration of chemotherapy.The amount of ctDNA.Metastatic recurrence.

### Eligibility criteria

2.4

The participants should meet the inclusion criteria in order to be enrolled in the study (see Table 1). Only adult (over 18 years of age) female patients diagnosed for the first time with non-metastatic TNBC will be recruited. The eligible patients must be treated with chemotherapy, surgery, and radiation therapy (RT). The lack of tumor sample from biopsy, necessary for the evaluation of TILs and the lack of blood test results at diagnosis will render the inclusion impossible.

**Table 1 T1:** Inclusion and exclusion criteria of the PERCEPTION trial.

Inclusion criteria	Exclusion criteria
Female	Unavailable biopsy tumor samples
Age ≥18 yr	Unavailable blood test results at the time of diagnosis
Primitive, non-metastatic triple negative breast cancer, diagnosed histologically	Pregnant or breastfeeding women, vulnerable persons, adults under legal protection, or unable to give their consent, according to the L.1121-6 article of the Public Health Code
Treated with chemotherapy, surgery, and radiation therapy	
French language fluency	
Affiliation to social security	
Able to provide a signed informed consent form	

Patient may exit study prematurely following:

-Patient decision-Investigator decision-Patient death-Patient lost to follow-up

### Study design

2.5

Eligible patients will be selected out of a local database of TNBC patients and will be recruited during the first year following the end of RT. The data collected before inclusion, such as TILs evaluation at baseline and in the surgical specimen, as well as blood test results at different times (baseline, before surgery, before the start of RT, and 6 months after the end of RT) will also be analyzed. After inclusion in the PERCEPTION trial, patients will undergo 2 interventions. A blood test will be performed 12 months after the end of RT and another blood test will be performed at the time of the first metastatic recurrence, if applicable. WBC, ANC, ALC, APC, NLR, PLR, and ctDNA will be measured from these blood tests. The overall follow-up is 5 years (see Fig. 1).

**Figure 1 F1:**
[figure not shown]
Timeline of the patients’ treatment and follow-up. CT = chemotherapy, NACT = neoadjuvant chemotherapy, RT = radiation therapy. Patients are included in the trial 1 year after the end of radiation therapy, as indicated by the blue arrow.

### Recruitment

2.6

Recruitment will be carried out in the Jean Perrin Centre by an oncologist. After checking the inclusion and exclusion criteria, the study will be thoroughly explained to the patient by the oncologist, and a consent form will be signed by both.

The recruitment period will last 3 years, from October 2019 to October 2022; 90 patients are expected to be included. After enrolment completion, the primary objective will be analyzed. The overall follow-up for each patient is 5 years, if no metastatic recurrences occur.

### Data collection and management

2.7

Most of the data will be available and will have been collected at the time of enrolment:

Demographic data (age)Initial diagnosis of TNBC (date of diagnosis, histological characteristics of the tumor, hormone receptor and HER2 expression, TNM classification)Cancer treatment and response to the treatmentClinical characteristics of the tumor in the surgical specimenBlood test results at the time of diagnosis, before surgery, before the onset of RT, and 6 months post-RTTIL amount in the biopsy and in the surgical specimen

After patient enrolment, blood test results at 12 months post-RT and at the time of the first metastatic recurrence will be collected.

A comparison of the demographic and recurrence data of the recruited patients to those of eligible patients but not included in the study will be performed, to show that the studied population in this trial is no different from the general population of non-metastatic TNBC patients.

The assessment of TIL quantity will be independently performed by 2 breast pathologists. In case of the initial result discordance, the slides will be reviewed by both pathologists under a multi-headed microscope and the consensus will be reached after a concertation.

Tumor DNA mutations will be identified from tumor samples. Then, DNA will be extracted from the blood plasma and will be amplified by polymerase chain reaction (PCR), in order to select the DNA region carrying the mutation identified in the tumor sample and to measure the quantity of circulating tumor DNA.

Data will be collected and entered in the electronic Case Report Form (eCRF) by a Clinical Research Associate (CRA) in charge of the study, under the responsibility of the principal investigator.

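### The planned comparison with eligible non-included patients cannot show that the cohort matches the general non-metastatic TNBC population

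*Protocol article*

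**What the plan says.** Section 2.7 (Data collection and management) sets up a comparison of the "demographic and recurrence data of the recruited patients to those of eligible patients but not included in the study". Its purpose is "to show that the studied population in this trial is no different from the general population of non-metastatic TNBC patients". Age is the only demographic item in that section's list of data.

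Section 2.4 (Eligibility criteria) defines who counts as eligible: "The eligible patients must be treated with chemotherapy, surgery, and radiation therapy (RT". A biopsy sample must be available, and "the lack of blood test results at diagnosis will render the inclusion impossible". Table 1 adds "Able to provide a signed informed consent form".

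On timing, Section 2.5 (Study design) says that patients, selected from a local TNBC database, "will be recruited during the first year following the end of RT". The legend of Figure 1 says "Patients are included in the trial 1 year after the end of radiation therapy".

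Section 2.9 (Statistical analysis) sets alpha at 5% for hypothesis tests, promises effect sizes throughout, and justifies 90 patients by the primary correlation.

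**The concern.** The article fixes the conclusion of this check before any data are seen, and the design of the check does not allow that conclusion.

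- **Comparator.** The target named is all non-metastatic TNBC, but the comparison group has passed the same treatment and data filters as the recruits. Agreement between two groups selected in the same way says nothing about patients removed by that selection.
- **Inference.** Finding no difference is not the same as showing that there is none, least of all with a sample sized for another question.
- **Variables.** Age and recurrence are compared. Diagnostic NLR and TILs, the two primary endpoints, are not.
- **Timing.** Recruits are by definition alive at consent. Comparators need not be alive at the same point.

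What is at stake is the reach of the primary result. The primary objective concerns TNBC patients at diagnosis, yet entry depends on what happens between diagnosis and the period after radiation therapy. If this check is reported as passed, the NLR–TIL correlation will be read as applying to all non-metastatic TNBC, without support.

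**Working it through.** **1. The plan's own figure.** The check has no stated figure. The only sample size is 90, for a correlation of 0.3 with power 0.8 and alpha 0.05 (Section 2.9; two-sided assumed). For a Spearman coefficient on the Fisher z scale with variance factor 1.06:

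n = 1.06 × [(1.960 + 0.842)/atanh(0.3)]² + 3 = 1.06 × (2.802/0.3095)² + 3 = 1.06 × 81.93 + 3 = 89.8, so 90.

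Power at 90 = Φ(0.3095 × √(87/1.06) − 1.960) = Φ(0.844) = 0.801. The stated figure reproduces, but it belongs to the primary correlation and not to this check.

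**2. Who can appear in the comparison.** This step needs no assumed figures.

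| Patient with non-metastatic TNBC | Recruited | Eligible, not included |
|---|---|---|
| Died, progressed or stopped before completing chemotherapy, surgery and RT | no | no |
| No biopsy sample or no diagnostic blood results | no | no |
| Completed treatment, samples available, consented | yes | no |
| Completed treatment, samples available, not recruited | no | yes |

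The first two rows belong to the target population but to neither group. The comparison can speak only to the last two.

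**3. What a non-significant result would mean.** Assumptions not in the documents: 90 recruited with 20% recurrence, and m non-included with 30%. With a two-sided 5% test,

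power = Φ[(0.10 − 1.960 × SE₀)/SE₁], where SE₀ uses the pooled proportion and SE₁ the separate ones.

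Example, m = 60: pooled proportion = (18 + 18)/150 = 0.24; SE₀ = √[0.24 × 0.76 × (1/90 + 1/60)] = 0.0712; SE₁ = √(0.16/90 + 0.21/60) = 0.0726; power = 0.29.

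The half-width of the 95% CI, with 20% in both groups, is 1.96 × √[0.16 × (1/90 + 1/m)]. For age, power to detect a difference of 0.3 SD is Φ[0.3/√(1/90 + 1/m) − 1.960].

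| m | Power, 20% vs 30% | CI half-width (points) | Power, age 0.3 SD |
|---|---|---|---|
| 30 | 0.22 | 16.5 | 0.30 |
| 60 | 0.29 | 13.1 | 0.44 |
| 90 | 0.34 | 11.7 | 0.52 |
| 180 | 0.41 | 10.1 | 0.64 |

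Other assumed rates over the same range of m give power of 0.32 to 0.55 (10% vs 20%) and 0.20 to 0.38 (25% vs 35%).

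For scale, consider a formal demonstration of similarity by two one-sided 5% tests, with 80% power and true recurrence of 20% in both groups. It needs 2 × 0.2 × 0.8 × (1.645 + 1.282)²/margin² per group: about 275 for a margin of ±10 points and 122 for ±15 points.

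**4. Time origin.** The article does not say how recurrence time is counted, so this is an illustration only. Assume that both groups share one constant hazard, that recruits are recurrence-free at entry t years after RT, and that both are followed to 5 years after RT. With true 5-year recurrence R, λ = −ln(1 − R)/5 and recruits show 1 − exp[−λ(5 − t)].

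- R = 20%, t = 0.5: 18.2%, which is 1.8 points lower.
- R = 40%, t = 1: 33.5%, which is 6.5 points lower.

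A gap of this kind would arise from the entry rule alone if comparators were counted from the end of RT.

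**The case against.** The strongest reply is that this is one overclaiming sentence about an ancillary check. The check does not feed the primary analysis (Section 2.10). Effect sizes are promised throughout, so reliance on a bare P-value is not certain. The number of comparators and the recurrence rates above are assumed, and a margin or a rule for counting time may stand in a full protocol or SAP. All of this is fair, and it limits the point. It does not remove it: the purpose of the check is stated in this text, and no analysis rule can recover patients whom the comparator excludes.

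Three stronger readings are tempting but not supported.

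- **Recurrence must differ by construction, by a computable amount.** The article gives no time origin or follow-up for non-included patients, so bias follows only if no common origin is used. Recruits must be alive to consent; no listed criterion requires them to be relapse-free. A specific inflation of recurrence-free survival therefore cannot be derived from the documents.
- **Everyone who relapses or dies before enrolment is left out.** This holds for losses before treatment completion. Recurrence after RT is not an exclusion criterion in Table 1, so patients lost between RT and consent may be among the eligible non-included. If they are, they contribute to the timing problem and not to the omission; these are different patients.
- **Selection makes the stated power of 0.8 wrong.** Section 2.9 states power for an effect of 0.3 and does not say that 0.3 is the correlation in unselected patients. Selection on both markers could weaken the correlation, but by how much depends on hazard ratios and loss rates that the documents do not give.

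**Conclusion.** The point holds in limited form. The comparison in Section 2.7 cannot show that the cohort is no different from the general non-metastatic TNBC population. The main ground is the comparator, which follows from Sections 2.4 and 2.7 without any assumed figure: even identical groups would not support the claim. The second ground is that a non-significant difference would be weak evidence. Power of 0.22 to 0.41 and CI half-widths of 10 to 17 points rest on the assumed recurrence rates and on 30 to 180 comparators. The third ground, bias from unequal time at risk, is conditional on how recurrence is counted.

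The two statements of entry time, Section 2.5 and Figure 1, must be reconciled because they determine how much survival time is guaranteed to recruits. The sample size for the primary correlation is not in question. The change should be made because it alters what the trial may conclude about generalisability.

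**What to change.** 1. In Section 2.7, replace the aim of showing no difference with a description of differences between groups, reported with 95% confidence intervals.
2. Extend the comparator to all non-metastatic TNBC patients in the local database diagnosed in the same period, with counts by reason for non-inclusion (died, progressed or stopped before completing treatment; no biopsy; no diagnostic bloods; not approached; declined).
3. Add diagnostic NLR to the variables compared, and TILs where already scored. Diagnostic blood results are an eligibility condition, so NLR should be obtainable for every eligible non-included patient.
4. Compare recurrence as time to event from a common landmark, or with delayed entry for recruits, once Section 2.5 and Figure 1 agree on the time of inclusion.
5. If differences appear, state the target population as treatment completers. Even the wider comparison describes one centre.

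An inverse-probability-weighted sensitivity analysis of the primary correlation is optional. It would need covariates for patients outside the trial, and the article does not say whether these exist.

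The cost is a wider extract from an existing database, some extra data work, and a more modest generalisability claim. No visit, sample or treatment changes. How complete the database is for patients who did not finish treatment is not stated and should be checked first.

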### Data confidentiality

2.8

Data collected and transmitted to the promoter by the investigators will be anonymized. Study data will not contain any names or other personal identifiers such as addresses. Patients included in the trial will be identified by a code specific to this trial. The investigator will have access to the correspondence table between the patient's last name, first name, date of birth, and the code assigned in the trial.

### Statistical analysis

2.9

Given the scarcity of data in the literature concerning the correlation between TILs and NLR, our goal is to recruit as many patients as possible. A sample size of 90 patients would allow us to show an average effect size of 0.3 (with a 0.8 power and a 0.05 alpha risk). According to preliminary studies (not published), the variables present enough variability to allow for the detection of a correlation.

Statistical analysis will be performed with R software (v3.6 or newer, R-Project, GNU GPL, http://cran.r-project.org/). Each variable of interest will be expressed by conventional statistical summaries: the quantitative variables will be expressed through the most relevant position indicator (mean, median, quartiles, range) and dispersion indicators (standard deviation, interquartile range), and qualitative variables will be expressed by counts and percentages for each level.

Normality of continuous variables will be investigated and we will perform a description of the dependencies of the pairs of variables, where relevant. For hypothesis testing, alpha risk will be set at the conventional 5%, *P*-value corrections will be made for multiple comparisons, and effect sizes will be systematically specified. If relevant, post-hoc tests and comparisons in subgroups will also be performed for exploratory purposes and with adjustment for multiple testings.

